### Vascular function

2.16

Vascular function will be measured in the four extremities, the cardio-ankle vascular index, the brachial-ankle pulse wave velocity and the ankle-brachial index at rest using the Vasera VS-2000 Vascular Screening System (Fukuda Denshi, Japan).

### Physical fitness components

2.17

Cardiorespiratory fitness will be assessed through a graded stress test using ergospirometry (Cosmed, K5 b2, Italy) on a cycle ergometer (Excalibur Sport 925909, Lode, The Netherlands). A standardized protocol for children and adolescents will be followed, including a warm-up phase, a systematic increase in resistance (10 or 20W per minute) until reaching maximum exertion, and then transitioning into the recovery phase. Peak oxygen consumption (VO_2peak_) and metabolic equivalents (METs) will be determined.

Muscular fitness will be measured by handgrip strength using the Takei III Smedley Type Digital Dynamometer, which provides an estimate of an individual’s overall strength. Then, EGYM Smart Strength machines (developed by eGym® GmbH in Munich, Germany) will be used to measure both maximal strength and muscular power in upper (chest and arms) and lower (legs and hip) extremity muscles. Handgrip strength assessment will take place in weeks 12 and 24.

### Physical activity, sedentary time, and sleep duration by accelerometers

2.18

The volume and intensity of physical activity will be measured using a GENEActive triaxial accelerometer (ActivInsights) worn on the wrist of the nondominant hand. The accelerometers will be programmed to measure at a frequency of 87.5 Hz over a period of nine consecutive days (36). The research team will determine that sampling 86 times per second is sufficient to capture the majority of movements performed by patients. The accelerometer data will be extracted using GENEActiv PC Software (version 3.3) and processed and analyzed using the R package GGIR (37). Waking wear time for valid cases represented children and adolescents with at least seven days and at least 10 hours of waking wear time in a 24-hour period, including one weekend day, will be considered for analysis. Validated cut points will be used to determine different physical activity variables (38, 39): sedentary activity (for children: 0–56.3 mg; for adolescents: 0–50 mg), light physical activity (for children: 56.3–191.6 mg; for adolescents: 50–150 mg), moderate physical activity (for children: 191.6–695.8 mg; for adolescents: 150–500 mg), and vigorous physical activity (for children: >695.8 mg; for adolescents: >500 mg). Moderate-to-vigorous physical activity will be defined as activities for which at least 80% of 1 minute of time satisfies the moderate physical activity threshold criteria (i.e., 191.6 mg for children and 150 mg for adolescents), in order to remove signals related to random wrist movement (40). The duration of sleep will also be determined. According to van Hees et al. (41) a sleep algorithm will be used to detect sleep and wake between bedtime and get uptime.

### Sleep quality and duration

2.19

The Pittsburgh Sleep Quality Index (PSQI) will be used. It evaluates seven established aspects of sleep quality: subjective sleep quality, time taken to fall asleep, duration of sleep, sleep efficiency, sleep disturbances (such as nightmares, pain, or feeling too hot or cold), use of sleep medication, and daytime dysfunction (42).

### Sedentary behaviors (screen time)

2.20

Sedentary behaviors will be assessed using the Youth Leisure-Time Sedentary Behavior Questionnaire (YLSBQ). Participants will report the time spent on TV, video games, computers, and mobile phones on both weekdays and weekends. To calculate the weighted average daily sedentary screen time for each behavior, we will use a 5:2 ratio. For instance, this calculation involves multiplying the daily TV viewing time on weekdays by five, the daily TV viewing time on weekend days by two, and then dividing the sum by seven (43). The total daily sedentary screen time will be determined by summing the durations of various daily screen time activities. Additionally, total screen time for both weekdays and weekends will be calculated.

### Self-reported physical activity

2.21

The measurement of physical activity will be based on the following question: “Typically, how many days will you engage in physical activity for a total of at least 60 minutes?”. Response options will range from 0 to 7 days per week, in 1-day increments. Physical activity will be defined as less than 60 minutes of physical activity per day on at least 7 days per week (44). The measurement of muscle-strengthening activities will be based on the following questions: “In the past 7 days, how many days did you perform exercises to enhance or tone your muscles, such as pushups, sit-ups, or weightlifting?” The response choices ranged from 0 to 7 days.

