## Introduction

1

Type 1 diabetes mellitus (T1DM) imposes a substantial burden on children and adolescents worldwide. According to estimates from the International Diabetes Federation (IDF), 1.2 million individuals under age 20 have T1DM globally (1). Not maintaining optimal glycemic control is associated with chronic health issues later in life. However, achieving and sustaining appropriate glycemic control poses a significant challenge for young individuals with T1DM, particularly during the transition from childhood to adulthood. Inadequate glycemic control in T1DM patients can lead to long-term complications including cognitive dysfunction (2), cardiovascular disease (3), diabetic neuropathy (4), diabetic retinopathy (5), chronic kidney disease (6), diabetic foot ulcers (7), and dry skin (8). While technology has enhanced self-management capacity (9), novel strategies that are accessible and cost-effective are urgently needed to improve glycemic control in young T1DM patients.

The American Diabetes Association (ADA) recommends that individuals under 20 years old with diabetes engage in 60 minutes of moderate to vigorous aerobic physical activity daily. This should be paired with vigorous muscle-strengthening and bone-strengthening activities at least three days per week (10). However, children and adolescents with T1DM are less active, more sedentary, and less fit than their healthy counterparts (11). A recent meta-analysis showed that exercise training has a moderate effect on reducing glycated hemoglobin (HbA1c) and insulin dose per day in youths with T1DM (12). Specifically, resistance training seems to be one of the most effective strategies for improving glycemic control among children and adolescents with T1DM (13). In adults, resistance exercise has proven efficacy in minimizing exercise-induced hypoglycemia risk in T1DM (14, 15). However, lack of awareness and fear of hypoglycemia can discourage young people from participating in physical activities, especially resistance exercise (16). This highlights the need for new technologies to support the T1DM population in managing hypoglycemia situations and promoting exercise.

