### 24-h hour movement guidelines

2.22

Participants who engaged in at least 60 minutes of moderate to vigorous physical activity per day and at least three days of muscle-strengthening activities, had less than two hours of recreational screen time per day, and achieved uninterrupted sleep for 9 to 11 hours per day (for children) or 8 to 10 hours per day (for adolescents) will be categorized as meeting the comprehensive 24-hour movement guidelines (45).

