### Adherence to the Mediterranean diet

2.27

We will use the Mediterranean Diet Quality Index for Children and Teenagers (KIDMED) index to assess adherence to the Mediterranean diet (52). The KIDMED index ranges from 0 to 12 and is based on a 16-question test. Unhealthy characteristics associated with the Mediterranean diet are assigned a score of -1 point, while healthy characteristics receive a score of +1 point.

The sum of all scores obtained from the KIDMED test will be utilized to classify individuals into three different levels: (a) optimal Mediterranean diet (>8 points), (b) improvement needed to align with Mediterranean dietary patterns (scores ranging from 4 to 7), and (c) very low diet quality (≤3 points).

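### Two secondary-measure scoring rules cannot be used as written: self-reported physical activity is defined by falling short of 60 minutes, and a KIDMED score of 8 belongs to no diet class

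*Protocol article*

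**What the plan says.** **Self-reported physical activity (protocol article, section 2.21).** The item reads "Typically, how many days will you engage in physical activity for a total of at least 60 minutes", and "Response options will range from 0 to 7 days per week, in 1-day increments". The answer is thus a count of days on which the 60-minute mark is reached. The derived category follows: "Physical activity will be defined as less than 60 minutes of physical activity per day on at least 7 days per week".

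Two other places set the activity threshold in the opposite direction. Section 2.22, on the 24-hour movement guidelines, credits "Participants who engaged in at least 60 minutes of moderate to vigorous physical activity per day". The Introduction reports a recommendation that young people with diabetes "engage in 60 minutes of moderate to vigorous aerobic physical activity daily".

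**KIDMED (section 2.27).** "The KIDMED index ranges from 0 to 12 and is based on a 16-question test". Unhealthy characteristics "are assigned a score of -1 point, while healthy characteristics receive a score of +1 point". The total is then used to place each child in one of three levels: "a) optimal Mediterranean diet (>8 points), (b) improvement needed to align with Mediterranean dietary patterns (scores ranging from 4 to 7"), and a lowest level for scores of 3 or less.

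The abstract and the aims name 24-hour movement behaviors and diet among the secondary outcomes, and Table 1 lists both instruments. Section 2.4 gives compliance with physical activity guidelines as one aim of the intervention.

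**The concern.** Both sentences are scoring rules that an analyst would program, not background text.

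The activity rule attaches the label of physical activity to children who fall short of 60 minutes. Coded as written, it would count a child who never reaches 60 minutes as active and a child who reaches it every day as not active. The reported percentage would then describe something other than its label, on a behaviour that the app is meant to improve.

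The KIDMED rule is meant to classify every child but cannot. A child who scores 8 must either be left out of the three-level result or be given a class chosen later, possibly once the data have been seen. The gap lies just below the top class, so where 8 is placed affects the proportion rated as having an optimal diet.

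**Working it through.** No power or sample-size formula applies. The check passes every possible answer or score through the stated rule.

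**1. Physical activity**

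Inputs, all from section 2.21: d = reported days with at least 60 minutes, d = 0, 1, ..., 7. Days below 60 minutes = 7 − d.

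- Rule as written: active if 7 − d ≥ 7, that is, d = 0.
- Rule A, meeting the recommendation (at least 60 minutes on all 7 days, the direction of section 2.22 and the Introduction): d ≥ 7, that is, d = 7.
- Rule B, inactivity (60 minutes not reached on all 7 days): d < 7, that is, d = 0 to 6.

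| d | As written: active | Rule A: meets recommendation | Rule B: inactive |
|---|---|---|---|
| 0 | yes | no | yes |
| 1 to 6 | no | no | yes |
| 7 | no | yes | no |

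The rule as written gives the active label to the least active answer only and withholds it from the most active one. Rules A and B are exact complements, so either is usable with the right label. The rule as written is the complement of neither: its complement is d = 1 to 7.

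This limits what can be said about direction. A child who moves from 0 to 3 days changes category under the written rule but not under rule A. A child who moves from 5 to 7 days changes under rule A but not under the written rule. Only a move between 0 and 7 changes both, in opposite directions.

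**2. KIDMED**

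Inputs, all from section 2.27: items score −1 or +1, so totals are whole numbers. The stated range is 0 to 12, which gives 12 − 0 + 1 = 13 possible scores.

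- Lowest class (3 or less): 0, 1, 2, 3, which is 4 scores.
- Middle class (4 to 7): 4, 5, 6, 7, which is 4 scores.
- Top class (above 8): 9, 10, 11, 12, which is 4 scores.

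4 + 4 + 4 = 12 of the 13 scores are classified. The one left over is 8.

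If the top class began at 8, it would hold 5 scores, and 4 + 4 + 5 = 13. If the middle class ran from 4 to 8, the count would also be 4 + 5 + 4 = 13. Either choice closes the gap, and the arithmetic does not favour one over the other.

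**The case against.** The strongest reply is that these are drafting slips with little consequence, and much of it stands.

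- **The label may be wrong, not the threshold.** The sentence may simply have lost a prefix, with inactivity intended. The document does not settle this, so it would be wrong to assert that the inequality is the error.
- **Other measures do not depend on the slip.** The 0-to-7 day count is still recorded. Section 2.18 measures activity by accelerometer with cut points in the right direction, and section 2.22 states its own correctly directed criterion. No section makes the self-reported dichotomy a named endpoint.
- **KIDMED totals are kept.** A child who scores 8 loses a class label, not data. Section 2.36 plans mixed models for each dependent variable, and the summed score can be analysed in that way.
- **An attentive analyst would probably notice.** Someone reading section 2.21 alongside section 2.22 is unlikely to code 0 days as active.

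Two stronger readings are tempting. A reader might infer that the activity rule reverses the sign of the treatment comparison. It need not: the written rule picks out answer 0 and the recommendation picks out answer 7, while answers 1 to 6 are coded alike under both. A reader might also try to state how many children the KIDMED gap removes. The document gives no distribution of scores, so no such number is supported.

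The reply does not remove the point. Both rules are stated explicitly. One contradicts its own question, and the other cannot do what its section says it will do.

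**Conclusion.** Both rules are wrong as written, and this can be established from the protocol article alone. For self-reported activity, 1 of the 8 possible answers (0 days) earns the active label, and the answer that meets the recommendation (7 days) does not. For KIDMED, 1 of the 13 possible scores has no class.

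The size is small. Each slip affects a derived category of a self-reported secondary measure. The underlying day count and summed score, the accelerometer outcome and the 24-hour guideline criterion are untouched, as are the primary outcome and the sample size. The conclusion rests on two assumptions: that the rules would be applied literally, and that KIDMED totals are whole numbers, which follows from the stated item scoring. Whether the threshold or the label is wrong in section 2.21, and which class should take a score of 8 in section 2.27, cannot be decided from the document.

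**What to change.** Make both changes before analysis.

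1. **Section 2.21.** The authors should confirm which meaning was intended and reword accordingly. One option is to define meeting the recommendation as at least 60 minutes on all 7 days (answer 7). The other is to rename the category physical inactivity and define it as the complement (answers 0 to 6).
2. **Section 2.27.** Make the classes exhaustive by assigning a score of 8 to one of them according to the cited instrument, before the data are seen. Starting the top class at 8 is one example; the authors should check it against the source.

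The cost is two reworded sentences and the matching lines of analysis code. No questionnaire, visit or data field changes.

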### 24-h hour movement guidelines

2.22

Participants who engaged in at least 60 minutes of moderate to vigorous physical activity per day and at least three days of muscle-strengthening activities, had less than two hours of recreational screen time per day, and achieved uninterrupted sleep for 9 to 11 hours per day (for children) or 8 to 10 hours per day (for adolescents) will be categorized as meeting the comprehensive 24-hour movement guidelines (45).

### Self-reported physical fitness

2.23

The International Fitness Scale (IFIS) is designed for assessing self-reported physical fitness. This scale consists of five elements that employ a 5-point Likert scale to inquire about the children’s general perception of their physical fitness, as well as their perception of their cardiorespiratory fitness, muscular fitness, speed-agility, and flexibility relative to their peers. The Likert scale provides choices ranging from very poor to poor, average, good, and very good physical fitness (46, 47).

### Inadvertent hypoglycemia

2.24

The perception of hypoglycemia will be measured using the Clarke test, which consists of eight questions with different possible answers, A score greater than three reflects impaired awareness of hypoglycemia (48).

### Sociodemographic information

2.25

Self-reported variables will be collected via a questionnaire administered to the participants’ parent(s) or guardian(s). The questionnaire will cover participant details such as school, sex, age, birthplace, race/ethnicity, and language spoken at home. Additionally, it will include information about the parent(s) or guardian(s), including birthplace, age, education level, professional qualifications, employment status, job role, monthly income, household location, neighborhood, and birth weight.

### Psychological assessments

2.26

To evaluate the HRQL in context of a chronic illness, the Spanish version of the “Questionnaire for Young people with Diabetes” (DISABKIDS) will be used (49). This questionnaire comprises 12 questions about how a patient has felt in the last four weeks that require answers on a 5-point Likert scale from 1 (never) to 5 (always).

We will also assess the HRQL using the Screening for and Promotion of HRQL in Children and Adolescents (KIDSCREEN-10) (50). This is a generic 10-item unidimensional instrument that focuses on the functional, mental, and social aspects of well-being in children and adolescents aged 8-18 years. The instrument will consist of the following items, starting with “thinking of last week, have you: 1) felt physically fit and well, 2) felt full of energy, 3) felt sad, 4) felt lonely, 5) had enough time for yourself, 6) been able to do the things you want in your free time, 7) felt treated fairly by your parent(s), 8) had fun with your friends, 9) got along well at school, 10) been able to pay attention at school?”. For each item, participants will provide their responses on a five-point scale, ranging from “never” to “always” or from “not at all” to “extremely”.

We will also assess subjective well-being using the “*Cuestionario Unico de Bienestar Escolar*” (CUBE) (51). The CUBE questionnaire consists of 5 items that assess various aspects of life satisfaction. All these variables will be measured using a 10-point Likert scale ranging from 0 to 10 (0 = totally disagree, 10 = totally agree).

In terms of positive affect, the scale includes five items assessing emotions such as happiness, joy, cheerfulness, contentment, and fun. Additionally, there are five items evaluating negative affect, which encompasses feelings of humiliation, annoyance, irritation, bitterness, and sadness. The scale follows a bifactorial structure with five items per factor.

### Adherence to the Mediterranean diet

2.27

We will use the Mediterranean Diet Quality Index for Children and Teenagers (KIDMED) index to assess adherence to the Mediterranean diet (52). The KIDMED index ranges from 0 to 12 and is based on a 16-question test. Unhealthy characteristics associated with the Mediterranean diet are assigned a score of -1 point, while healthy characteristics receive a score of +1 point.

The sum of all scores obtained from the KIDMED test will be utilized to classify individuals into three different levels: (a) optimal Mediterranean diet (>8 points), (b) improvement needed to align with Mediterranean dietary patterns (scores ranging from 4 to 7), and (c) very low diet quality (≤3 points).

### Food consumption

2.28

Food frequency consumption will be assessed some food frequency questionnaires (FFQs) for the Spanish young population (53, 54). These FFQs includes several items groped into 17 food groups and were previously validated for its use among children (54) and adolescents (53) in a self-reported way. Subsequently, macronutrients, micronutrients, total energy consumption and other diet-related variables will be estimated. On the other hand, adherence to the healthy and sustainable dietary recommendations (e.g., fruits, vegetables, nuts, etc.) of the Ministry of Consumer Affairs of the Government of Spain will be determined (55).

### Screening for eating disorders

2.29

To evaluate disordered eating, the modified SCOFF (mSCOFF) questionnaire will be used. This screening tool consists of five straightforward questions and can be conveniently incorporated into a routine check-up. It has proven to be reliable and valid in its assessment of eating disorders among children and adolescents with T1DM (56).

### App usability

2.30

We will use the Spanish Version of the User Version of the Mobile Application Rating Scale (uMARS) (57), that will serve as a comprehensive and objective measure of app usability, consisting of 20 items. Each item is assessed using a 5-point scale, ranging from 1 (inadequate) to 5 (excellent). The uMARS will be structured into four subscales: engagement, functionality, aesthetics, and information quality. Subscale scores will be calculated as the average of their respective items, and the mean of these subscale scores will provide an overall app quality score.

### Participant timeline

2.31

Eligible and consenting participants will complete a baseline assessment. The intervention group will then be allocated to a 24-weeks exercise training program using the Diactive-1 App. The control group will continue standard care. Outcomes will be assessed at baseline (T0), 12-week (T1) and after the 24-week intervention period (T2) (**Table 2**).

**Table 2 T2:** Schedule depicting the enrollment and interventions for the Diactive-1 Study in accordance with the SPIRIT 2013 guidelines ^26^.

TIMEPOINT	STUDY PERIOD				
	Enrolment	Allocation		Post-allocation	
	*-t_1_ *	0	*Baseline* *(T0)*	*T_1_ * * _(12 weeks)_ *	*T_2_ * * _(24 weeks)_ *
ENROLMENT:					
Eligibility screen	X				
Informed consent	X				
Allocation		X			
INTERVENTIONS:					
*Diactive-1*		X			
*Waiting-list control group*		X			
ASSESSMENTS:					
*Daily insulin dosage requirement*			X	X	X
*Glycemic control (time in range, glucose coefficient of variation, number of hypoglycemic and hyperglycemic events)*			X		X
*Cardiovascular biomarkers (of fasting glucose, glycated hemoglobin, triglycerides, high-density lipoprotein cholesterol, low-density lipoprotein cholesterol, apolipoproteins, alanine aminotransferase, and aspartate aminotransferase)*			X		X
*Anthropometric parameters (body weight, standing and sitting height)*			X		X
*Sexual maturation and peak height velocity*			X		X
*Body composition parameters (total body fat, lean mass, subcutaneous and visceral adiposity, bone mineral content and density)*			X	X	X
*Heart rate variability*			X		X
*Vascular function*			X		X
*Physical fitness components (cardiorespiratory and muscular fitness)**			X	X	X
*Physical activity, sedentary time, and sleep duration by accelerometers and questionnaires **			X	X	X
*Sleep quality*			X		X
*Inadvertent hypoglycemia*			X		X
*Psychological assessments (Health-Related Quality of Life and subjective well-being)*			X		X
*Diet (adherence to the Mediterranean diet and food consumption)*			X		X
*Eating disorders*			X		X
*App usability*					X

* It will only evaluate handgrip strength and accelerometer-based physical activity at 12-week mark. T, represents a time-point.

